### Qualitative study

An assistant research fellow will coordinate with the investigators in conducting semi-structured in-depth interviews following the intervention to evaluate participant experiences in the trial (94, 95). As they finish the trial, the participants will be asked if they would consider this additional interview and be enrolled sequentially until numbers are met. The interview will explore experiences and perceptions regarding interventions based on the theoretical framework of acceptability. These would be recorded with the consent of the participants. The aims of this interview include exploring the participants’ experiences regarding the barriers and facilitators in participating in the trial. In addition, the interview aims to assess the acceptability of the research procedures, including the intervention, preferences for the study site, the perceived value of the study, and the acceptability of interventions as potential clinical treatments for managing knee OA. Furthermore, the interview seeks to explore the perspectives of Māori people on assessment and treatment practices that align with their cultural worldview (95). Māori is treated as an important subgroup and are selected and interviewed separately. We aim to interview five people per group with a purposeful sample of Māori participants from each group. The participants in the usual care group will also be interviewed to explore their experiences participating in the trial, including the acceptability of the assessment procedures.

## Secondary outcomes

Table 2 presents the outcome domain and constructs, together with a brief description of the measurement tools used to measure the constructs and the measurement time points (96–127). All outcomes are well-established, reliable, and validated constructs in people with persistent pain (predictors of pain and disability) and are recommended for clinical trials of chronic pain and knee osteoarthritis (96–98, 120). Each assessment session will last for a maximum of 2 h, including completing the questionnaires and undergoing testing.

### Outcome assessor and blinding

A research assistant who will be blinded to the groups will collect the secondary outcomes at baseline, immediately post-intervention, and 3 months post-intervention. The effectiveness of blinding will be measured. The self-report questionnaires will be administered using the Qualtrics data management system. The participants will complete the questionnaires in two parts: at home and in person during the assessment sessions.

Pain and physical function measures will be measured using validated questionnaires in people with knee OA (99–102). All participants will perform the minimum physical performance core set (sit-to-stand, 30-s chair stand test, and walking short distances) as recommended by the Osteoarthritis Research Society International (102). A short physical performance battery (SPPB) will be administered that includes standing balance tasks. Pain intensity during each physical performance will be recorded using a numerical 0–100 numeric rating scale (0 = no pain, 100 = the most intense pain imaginable) (102, 132): All participants will be asked to perform a 6-min walk test (6MWT) to derive the Sensitivity to Physical Activity (SPA) index. The participants will be asked to rate their discomfort before the 6MWT and every minute of walking. The SPA index will be derived by subtracting baseline pain ratings from their greatest pain ratings for each trial. The European Quality of Life-5 Dimensions scale will be used to assess health-related quality of life (104). Depression, anxiety, and stress will be recorded, as well as the occurrence of pain catastrophising thoughts, pain self-efficacy, positive and negative affect, emotion regulation, and elements of mindfulness and coping levels (106–112). Sleep quality and physical activity levels will be measured. Following the training, the participants' perceptions of change (−5 = much worse, through 0 = unchanged, to +5 = completely recovered) in their symptoms will be measured using the global rate of change scale (99) Visual analogue scales (0–10) will be used to measure the overall acceptability, burden, perceived effectiveness, ethicality, culturally acceptable, the research team's trustworthiness and knowledge, and the likelihood of negative side effects of training. The credibility/expectancy questionnaire will measure the treatment expectancy and rationale credibility of the interventions tested (113, 114). The level of engagement with the training sessions will be recorded using a 10-point ordinal items scale, where 1 = least engaged and 10 = highly engaged—level of motivation. For the EEG-NF group, an adapted version of the Current Motivation-Brain Computer Interference (QCM-BCI) questionnaire will be used to assess the level of motivation for participation in the training (114). The Osteoarthritis Cost-and-Consequences questionnaire will be used to record healthcare use/expenses during the 3-month period prior to the study and the 3-month period post-intervention (105).

### Cardiovascular measures

The resting heart rate and beat-to-beat R-R interval will be measured using a Polar V800 HR monitor and a Polar H10 chest Pro Strap for a duration of 7 min, with a resolution of 2 ms. Blood pressure and respiratory rate will be measured. Raw heart rate and R-R interval time series data will be downloaded from the Polar flow software for further processing and analysis. Kubios software will be used to derive time and frequency domains of heart rate variability (HRV). Peripheral oxygen saturation will be monitored and recorded (123, 124).

**Quantitative sensory testing** procedures will be administered following the guidelines (115–122).

An algometer (AlgoMed, Medoc, Ramat Yishai, Israel) will be used to measure three trials of pressure pain threshold (PPT) over the two regions (index knee and non-dominant wrist) in random order. The mechanical temporal summation (MTS) procedure will be assessed twice using a nylon monofilament (Semmes monofilament 6.65, 300 g) under two contexts: at rest and during EEG recordings. Ten repetitive contacts will be delivered at 1 Hz. The participants rate the pain severity on an 11-point NPRS (0 = no pain to 100 = extreme pain) immediately after the first contact and rate the greatest pain intensity they experienced during 10 contacts. MTS is the difference between the NPRS scores after the first contact and the greatest pain scores. The average of two trials will be calculated. MTS will also be administered while EEG is being recorded. Pain intensity (NPRS 0–100) will be recorded following a single contact, and then the MTS will be administered in the following order: three trials of 10 contacts with 20 s rest period between trials. The overall pain intensity (NPRS 0–100) experienced during the three trials will be recorded following the completion of EEG recordings.

The conditioned pain modulation (CPM) procedure will be administered according to the published recommendations (98, 115) to measure the efficiency of the endogenous pain modulatory system. The conditioning stimulus involves the participants submerging their dominant hand in a cold water (−5°) bath for 2 min (maximum period) or until it is too uncomfortable. Pain intensity during the conditioning stimulus will be recorded on a 11-point NPRS (0 = no pain to 100 = extreme pain) at every 15 s intervals (98). The test stimulus involves measuring the suprathreshold PPT (pain40) at the tibialis anterior muscle over the non-dominant leg region. Two PPT (pain40) trials prior to exposure to the conditioning stimulus and three trials of PPT (pain40) trials at 30, 60, and 90 s following the conditioning stimulus will be recorded. The CPM will be determined by calculating the percent change score for each time point. Heart rate and blood pressure will be monitored for safety reasons.

For the collection, processing, and analysis of EEG data (125–127), the SynAmps RT Amplifier (Compudemics Neuroscan) will be used to capture resting-state EEG data for 10 min while the participant is seated in an upright position in a quiet room with closed eyes. The raw EEG signals will be processed according to our previous work (125–127). Exact low-resolution brain electromagnetic tomography (eLORETA) software will be used to estimate the intracerebral electrical sources in the following frequency bands: infraslow (0.01–0.10 Hz), slow (0.2–1.5 Hz), delta (2–3.5 Hz), theta (4–7.5 Hz), alpha1 (8–10 Hz), alpha2 (10.5–12 Hz), beta1 (12.5–18 Hz), beta2 (18.5–21 Hz), beta3 (21.5–30 Hz), and gamma (30.5–44 Hz). The current source density (CSD) and functional connectivity (FC) will be calculated for the selected regions of interest (ROIs), namely, pregenual, sub-genual, prefrontal, cingulate, insular, and somatosensory cortices. MM and NF interventions have been studied previously and have demonstrated altering the activity of the ROIs chosen in this trial. The changes in the CSD of the selected ROIs and FC between ROIs will be analysed within and between groups.

## Quantitative data analyses plan

Descriptive statistics will be derived for primary and secondary outcome measures. The sample size estimation was not determined for primary outcomes since it is a feasibility trial. However, we aim to recruit a sample (20 participants per group, 60 in total) in 1 year in a single centre to provide sufficient data for assessing adverse events, feasibility outcomes, identifying operational issues, and estimating variability estimates of clinical pain outcomes.

**In the full clinical trial**, linear mixed models will be used to examine the differences in changes in the pain and physical function between groups to determine the effectiveness of interventions against usual care based on the randomised group (i.e., using an intention-to-treat approach). Group–time interactions will be used to assess between-group differences at 1 and 3 months following the intervention, with 3 months being the primary endpoint. Potential explanatory factors (which could include age, sex, BMI, duration, baseline pain severity, and depression scores) will be adjusted in the analysis. In this feasibility study, we will still perform these analyses (with no stratification or competing exposure variables included) to assess the study protocol, focusing on the uncertainty in estimated effects, not statistical significance. The following parameters will be used to determine the sample size in the full clinical trial: standard deviations (SD) and correlations between repeated measures of outcome measures derived from the feasibility trial. The full trial will have 80% power to detect a meaningful difference in the primary outcome (i.e., pain severity at 3 months). The minimal clinically important difference for pain severity (NPRS) is 1.8 using a two-sided (0.05) significance level. An attrition rate informed by the results of this feasibility study will be incorporated.

Qualitative data analysis (72): The interviews will be audio-recorded and fully transcribed. The General Inductive Approach will guide the analysis. The qualitative findings will provide important information regarding recruitment and retention in the trial and the acceptability of interventions. The results of the qualitative study will be published separately.

Māori analysis (70, 128–131): The journal and the interview data will be subjected to qualitative and inductive thematic analysis and Māori analysis, field notes collected by the Māori researcher, and interviews with Māori participants to ensure that the study reflects the values, beliefs, and cultural practices of the Tangata Whenua community towards broader objectives for Māori development. This will support the researcher in identifying factors related to the perceptions of the Māori participants, including the study site and setting, the overall value of the study, and the level of acceptability of interventions as potential clinical treatments for managing pain associated with knee OA. Overall, the interviews will provide deeper insights into whether assessment and training practices could be acceptable to a Māori worldview.

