### Study design

This feasibility study (71, 72) will be a double-blind (outcome assessor and all investigators), three-arm randomised control parallel trial with participants having an equal probability of being assigned to each arm. The study outcome measures will be collected at baseline, immediately post-intervention (4th week), and 3 months post-intervention.

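### The covariate-free group-by-time model gives wider intervals for the feasibility effects than a model that conditions on the baseline value already collected

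*Protocol article*

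**What the plan says.** All references are to the Protocol article, Quantitative data analyses plan, unless stated.

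- For the full trial, "linear mixed models will be used to examine the differences in changes in the pain and physical function between groups". The effect parameter is an interaction: "Group–time interactions will be used to assess between-group differences at 1 and 3 months following the intervention, with 3 months being the primary endpoint".
- The possible adjusters include the baseline value of the pain outcome: "Potential explanatory factors (which could include age, sex, BMI, duration, baseline pain severity, and depression scores) will be adjusted in the analysis".
- The feasibility trial repeats the analysis without covariates: "In this feasibility study, we will still perform these analyses (with no stratification or competing exposure variables included) to assess the study protocol". Its emphasis is on "focusing on the uncertainty in estimated effects, not statistical significance".
- Baseline is measured in everyone. Under Study design: "The study outcome measures will be collected at baseline, immediately post-intervention (4th week), and 3 months post-intervention".
- On size, "we aim to recruit a sample (20 participants per group, 60 in total) in 1 year in a single centre", with no calculation behind the number: "The sample size estimation was not determined for primary outcomes since it is a feasibility trial".

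The article does not define the variables that it leaves out as competing exposures. Since the exclusion follows directly on the list of adjusters, the natural reading is that baseline pain severity is among them. The article also does not say whether the baseline means of the three arms are free or held equal.

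**The concern.** A group-by-time interaction on three visits, with a free baseline mean in each arm, estimates the difference between arms in change from baseline. Randomisation makes the true baseline means equal, and this model does not use that fact. It subtracts the whole of any chance baseline difference, whereas regression to the mean means that only a fraction r of it carries over to follow-up. The estimate remains unbiased over randomisations, but it has more sampling variation than one that conditions on baseline.

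This matters here because the plan puts the weight of the comparison on how uncertain the effects are, not on tests. With 20 per arm the intervals are wide in any case. Part of that width can be removed with data that the trial already collects.

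**Working it through.** **No figure to reproduce.** The article gives no SD, no correlation and no calculated sample size; 60 is 3 × 20. The check therefore compares the precision of two analyses of the same data.

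**Inputs from the article.** n = 20 per arm, equal allocation, visits at baseline, 4th week and 3 months, 80% retention regarded as acceptable (about 16 per arm).

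**Inputs assumed.** Pain SD s = 2.0 on a 0–10 scale, the same at each visit; baseline-to-3-month correlation r from 0.3 to 0.8; complete data.

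**Standard error of a two-arm difference at 3 months**

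- Interaction with free baseline means (change-score contrast): s × sqrt(2(1−r)) × sqrt(2/n)
- Baseline as covariate, or baseline means constrained equal: s × sqrt(1−r²) × sqrt(2/n)
- Ratio of the first to the second: sqrt(2(1−r)/(1−r²)) = sqrt(2/(1+r)). Both s and n cancel.

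**Example, r = 0.5, n = 20.** sqrt(2/20) = 0.316. Free baseline means: 2.0 × 1.000 × 0.316 = 0.632, half-width 1.96 × 0.632 = 1.24. Adjusted: 2.0 × 0.866 × 0.316 = 0.548, half-width 1.07. Ratio sqrt(2/1.5) = 1.155.

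| Assumed r | Half-width, free baseline means | Half-width, baseline-adjusted | Ratio sqrt(2/(1+r)) |
|---|---|---|---|
| 0.3 | 1.47 | 1.18 | 1.240 |
| 0.5 | 1.24 | 1.07 | 1.155 |
| 0.7 | 0.96 | 0.89 | 1.085 |
| 0.8 | 0.78 | 0.74 | 1.054 |

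These use the normal quantile. A t quantile on 57 degrees of freedom gives 1.50, 1.27 and 0.98 against 1.21, 1.10 and 0.90 at r = 0.3, 0.5 and 0.7. With 16 per arm and r = 0.5, the half-widths are 1.39 and 1.20 (normal quantile), in the same ratio.

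**Simulation.** Linear mixed models were fitted to 250 simulated trials of 3 arms × 20 participants × 3 visits at each of r = 0.3, 0.5 and 0.7. The mean model standard error with free baseline means, divided by that with constrained means, was 1.238, 1.157 and 1.085, against 1.240, 1.155 and 1.085 in theory. The empirical SDs of the estimates are noisier but point the same way: 0.702, 0.618 and 0.502 with free means, against 0.592, 0.527 and 0.453 with constrained means. Covariate adjustment gave 0.591, 0.528 and 0.453, so the two remedies are equivalent here.

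**Does the direction depend on equal SDs?** Let the SD be s0 at baseline and s1 at 3 months. The per-person variance of change is s0² + s1² − 2·r·s0·s1, and the adjusted variance is s1²(1−r²). Their difference is (s0 − r·s1)², which is never negative. The size of the loss depends on the assumptions; its sign does not, apart from the small cost of estimating one slope.

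**The case against.** The strongest reply is that the article never says that baseline means are free. A model with those means constrained equal contains no covariate, so it fits the quoted sentence and loses no precision. How the mean structure is set up is also commonly left to a fuller document that is not shown. This stands in part: if that document specifies the constrained form, the point is closed. What the article itself fixes, however, is a covariate-free model of differences in change, and the usual form of that is the unconstrained one.

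A second reply is that omitting covariates with 20 per arm is a legitimate simplification in a feasibility trial. That is fair as to validity, and it limits the weight of the point. It does not answer the loss of precision, since the remedy needs no new data and about one degree of freedom.

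Several stronger readings are tempting and are not supported:

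- *Baseline is excluded altogether.* A comparison of follow-up values alone would widen the interval by 1/sqrt(1−r²): 5%, 15%, 40% and 67% at the four correlations. The article speaks of differences in change and of repeated-measure correlations, so it does not describe that model.
- *Uncertainty is misstated.* It is not. The standard error of the change contrast already reflects chance baseline imbalance, and the interval is correct for that estimator; it is only wider than it need be.
- *Sizing of the full trial is compromised.* The plan carries forward SDs and repeated-measure correlations. A marginal SD s and a baseline-to-follow-up correlation r give the adjusted SD as s × sqrt(1−r²), so these outputs already support a baseline-adjusted design.
- *Baseline would be used twice in the full trial.* The list of adjusters is only of possible factors, and baseline pain can be an ordinary covariate for physical function. The text does not commit to double use.

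**Conclusion.** The point holds as a matter of efficiency. Read in the usual way, the feasibility model gives a valid interval that is about 24% wider than necessary at r = 0.3, 15% at 0.5, 8.5% at 0.7 and 5% at 0.8. These percentages assume complete data, equal SDs over time and free baseline means. They do not depend on the SD or on the number per arm, but r is an assumption, as the article gives none. That baseline pain severity is among the dropped variables is inferred from the order of the two sentences and is not stated outright.

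The practical impact is modest. The primary outcomes are recruitment, compliance, retention and safety, and the article ties no progression decision to a treatment-effect interval. The change is still worth making, because it improves, at almost no cost, the quantity that the plan says it will focus on.

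**What to change.** Revise the sentence on the feasibility analysis so that it says how baseline enters, in one of two ways:

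1. The 4th-week and 3-month values are the responses, and the baseline value of the same outcome is a covariate; or
2. All three visits are responses, with the baseline means constrained equal across the arms.

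The other explanatory factors can stay out, as now planned.

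Continue to report the marginal SD at each visit and the baseline-to-follow-up correlations as the inputs for sizing the full trial. Do not replace them with the residual SD from the adjusted model alone. If a residual SD is quoted, apply no further correlation discount to it, since it already contains the reduction from baseline.

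The cost is one sentence in the analysis plan and, for the covariate form, one degree of freedom (two if the baseline slope may differ by visit). No further data, visits or participants are needed.

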### Criteria for termination of the study

If any unexpected serious adverse medical event or other incidents occur, the study or one of the arms of the trial will be discontinued. A serious adverse medical event is defined as any occurrence or effect that is life-threatening, including death, requiring hospitalisation, and significant disability. These medical events are considered very unlikely in this study due to the nature of the interventions.

## Discussion

Self-regulatory interventions can improve health outcomes in people with chronic pain (20, 22). The proposed feasibility clinical trial will provide evidence on the feasibility, safety, and acceptability of self-regulatory interventions such as mindfulness meditation training and electroencephalography neurofeedback training in people with knee OA. It is essential to establish the feasibility of conducting a randomised control trial to investigate the effectiveness of these novel interventions for managing chronic secondary musculoskeletal pain. Therefore, a feasibility trial has been designed to assess the factors that could influence the conduct of a fully powered clinical trial.

The recruitment rate is one of the primary outcomes of this feasibility trial. Based on our previous experience in EEG-NF studies (56, 64, 65), we anticipate a favourable response from the community of people with knee OA living in an urban centre in this trial. However, predicting the recruitment rate/enrolment in this trial is not straightforward. Several factors can contribute to a less-than-optimal recruitment rate in this trial. Some of these factors that may affect recruitment include the presence of concurrent trials recruiting people with knee OA; the biomedical beliefs (wear and tear) in people with knee OA (135) could preclude participation in a trial focused on mind–body interventions such as mindfulness meditation; the potential of planned study advertisements and community engagements in reaching the population of interest, including the Māori and Pacific populations, and the anticipated level of acceptability and perceived usefulness of these self-regulatory brain-based interventions by the community of people with knee OA (64) are also important considerations. Moreover, this trial involves a significant time commitment over a short period, which may be a barrier to participation, affecting recruitment rates. Moreover, other barriers, such as parking availability and time away from work/family/childcare, can influence participation rates (133, 134). As hypothesised, good compliance and retention rates (80%) in the active training groups are expected.

Improving the treatment of knee osteoarthritis and access to treatments will help reduce health inequity between the Māori and non-Māori population (128). A Māori investigator will apply a Māori-centric approach to research, drawing on Kaupapa Māori theory (130). The proposed clinical trial will foster whakawhanaungatanga (building relationships) with Māori stakeholders and incorporate practices aligned with a Māori worldview, ensuring culturally relevant and sensitive interventions. Qualitative interview data will guide researchers in developing and testing culturally sensitive interventions in a future clinical trial (95), including addressing the barriers to participating in a clinical trial, thus addressing the specific needs of the Māori community in the New Zealand context. There is still a risk of inadequate representation of Māori in this trial despite this clinical trial being designed to implement culturally appropriate study procedures.

Since it is a feasibility clinical trial (137), and the sample size for this trial was not estimated, the secondary clinical outcomes were not powered to detect treatment effects. However, as supported by previous literature (64, 65), positive trends in the secondary outcomes, including pain severity, interference, and physical function, are anticipated in people undergoing active training. We hypothesise that the up-training pgACC training protocol will increase the current density across the frequency spectrum in the pregenual anterior cingulate cortex in people undergoing neurofeedback training (56). We hypothesise a reduction in the somatosensory cortex activity following mindfulness meditation training, whereas greater activation at the rostral anterior cingulate, anterior insula, and orbitofrontal cortices is expected. We also hypothesise a reduction in the mechanical temporal summation pain scores, an increased pressure pain threshold, and positive conditioned pain modulation responses in the active training groups compared with those in the control group. The dosage of interventions tested in this trial was similar to that of previous trials, but it may not be enough to demonstrate long-term clinical outcomes (64, 65). A future fully powered clinical trial could consider having booster training sessions to assess medium- to long-term training effects on clinical outcomes.

Estimating a range of side effects (minor to adverse events) associated with exposure to the proposed self-regulatory training procedures is critical. We will record symptoms weekly using the Discontinuation-Emergent Sign and Symptom checklist (93). Based on the previous pilot trial, we observed no significant adverse events associated with NF training (64, 65). The brief mindfulness meditation protocol used in this trial has been thoroughly investigated in experimental acute pain conditions and people with pain. This is the first trial that will provide signs and symptoms that may be associated with this specific brief mindfulness meditation training protocol used in this trial (136).

The experienced research team trained the research assistants in administering the assessment procedures. The research team has trained the research assistant to provide training and help in troubleshooting as it arises. The trained RAs will offer training as reported in the TIDieR checklist. An expert investigator will assess the fidelity of the NF intervention administration (138). A clinical psychologist associated with the Centre for Mindfulness, University of Southern California trained the research assistant to offer MM to the participants. The MM training protocol is scripted and was adapted slightly for cultural sensitivity by the Māori investigator; hence, the fidelity assessment of delivering MM may not be essential.

The biopsychosocial outcome measures in this trial have been selected based on the recommended core outcomes for clinical trials of chronic pain (97, 98). In addition, a range of physiological measures were used alongside the clinical outcomes to explore the potential mediating mechanisms contributing to the effect of intervention (120). A future fully powered clinical trial could assess the psychological and physiological markers as mediators and moderators of treatment effects. Due to a range of outcome measures utilised in the trial, we anticipate that the participants will face a burden in terms of completing the questionnaires and undergo test procedures. However, this issue could be addressed by scheduling for some questionnaires to be completed at home and administering specific questionnaires in person (134).

The neurofeedback training protocol in this trial has been previously used and demonstrated a clinically meaningful descriptive trend in the clinical outcomes (65). High-quality evidence (55) suggests that EEG-NF training effectively induces clinically meaningful analgesia in people with chronic pain. The observed clinical effect following NF training could result from active ingredients, such as NF-induced alterations in brain area activity and the placebo effects associated with NF training (e.g., wearing a cap or listening to auditory feedback). Therefore, having a placebo group (wearing an EEG cap only) is not required as this is a feasibility trial assessing the clinical effectiveness of NF training against mindfulness meditation and usual care. In our trial, we believe that the active ingredient (change in the brain activity) induced by the EEG-NF training protocol and the placebo effects would collectively produce the treatment effects.

